### Study periods, duration of participation

Recruitment of volunteers will be organized in small groups to ensure (1) a higher adaptation of the study period to the participants' daily schedule, (2) more effective and easier sampling and immediate processing of the obtained biological samples. The study will consist of 3 periods (Figure 1, Figure 2):

#### 1. Verification period

Subjects who will give their consent to participate in the trial by signing the informed consent form and meet the inclusion/exclusion criteria of the study, will further receive a participant's set. The participant's set includes a general questionnaire, questionnaire on health and heredity developed by the LGDB, a copy of an informed consent document, a questionnaire on observed side effects, diet diary, tubes for microbiological sampling and microbial sampling protocol (translated questionnaires are available upon request). The participant's set includes all the necessary instructions, materials and documentation forms to independently conduct the activities intended during the clinical trial. During the verification period hematological and biochemical analysis will be conducted in order to evaluate the health status of the volunteer.

#### 2. Use of investigational drug

Only the volunteers whose biochemical analysis and the information filled in the general questionnaire still indicate on a compliance with the inclusion / exclusion criteria will continue to participate in the study. The study participants will use film-coated tablets of *Metformal* 850 mg twice daily (within the interval of 10 to 12 hours) for 7 days. In parallel, participants will be asked: (1) to document their nutrition in a previously issued diet diary on a regular basis, (2) to collect stool samples independently at home and (3) to donate blood samples on their scheduled visits.

During the study, participants will be asked to refrain from drastic lifestyle alterations and dietary changes, except for the activities required for the study.

### 3. Observational period

After a seven-day use of *Metforal* 850 mg, the participants will fill out the questionnaire on the observed side effects assessing the feeling of well-being during the study. The day after the last dose of *Metforal* 850 mg, the last blood and fecal sample will be collected.

Participants will be involved in the study for a duration of 13 days. Within the framework of the study seven visits to the investigator and one phone visit will be organized:

***1st visit.*** During the first visit the investigator will introduce the potential study participant with the course of the study, inform about possible risks and benefits and provide the informed consent form. After this visit, each potential participant will get acquainted with the informed consent form and make a decision on participation in the study.

***2nd visit - Study Day 1.*** Volunteers agreed on their participation in the study will submit a signed and dated informed consent form to the investigator. The investigator will evaluate the participants' compliance with the inclusion / exclusion criteria. In case of non-compliance, the reasons for the exclusion of the participant will be documented. During the visit, participants will receive a copy of the informed consent form signed by the participant and the investigator, instructions for stool sample collection, tubes for stool sample collection, diet diary form, general questionnaire, questionnaire on side effects, LGDB health and heredity questionnaire. During the visit, the investigator will carry out the biometric measurements necessary for the completion of LGDB questionnaire. Starting from this day, the participant will be asked to fill out the diet diary in paper or electronic format following the instructions given therein. During the verification period (see Figure 1), the participant will be asked to collect their first stool sample for the gut microbiome analysis, before starting the administration of metformin. The collection and storage of stool samples will be carried out in accordance with the procedure described in the stool sampling protocol. The participant will be asked to find the nearest E. Gulbis laboratory where venous blood samples (11 ml) for hematological and biochemical analysis will be collected. After receiving the results of hematological and biochemical analysis the investigator will evaluate the compliance of the study participant again.

***3rd visit - Study Day 4.*** Blood samples (7 - 13 ml) will be collected from the participant's at fasting-state for further genotyping, DNA methylation, RNA expression and metabolite analysis. Participants will deliver a filled general questionnaire previously collected stool samples. The investigator will provide each participant with 14 film-coated *Metforal* 850 mg tablets and re-instruct on the mode of administration, duration, dose, storage and return of the drug. The administration of *Metforal* 850 mg will begin.

**4th visit - Study Day 4.** 10 hours after the first dose of the *Metformal* 850 mg (before the second dose), blood samples (7 - 13 ml) from the study participant will be repeatedly collected for DNA methylation, RNA expression and metabolite analysis. Participants will be instructed to collect the second stool sample on day 5 of the study.

**5th visit - Study Day 6.** Participants will be asked to attend a control visit in order to obtain the information about the participant's well-being and evaluate their compliance with the study protocol. Participants will bring the stool samples collected on Day 5.

**6th visit - Study Day 11** (the day after the last intake of *Metformal* 850mg). Blood samples at fasting-state will be obtained for DNA methylation, RNA expression and metabolite analysis. If necessary, the participant will return the unused *Metformal* 850 mg tablets. Participants will be asked to collect a stool sample within this day.

**7th visit - Study Day 12,** The final inspection visit. Participants will bring the stool samples collected on Day 11, filled diet diaries and questionnaire on side effects. The participant of the study will be informed about the upcoming telephone call on the 13th day of the study.

**Phone call visit - Study Day 13.** The investigator will contact each participant by phone, making sure about the participant's well-being and any side effects observed. If necessary consultation of physician or other certified specialist will be recommended. The investigator will answer any question regarding the progress of the study and inform the participants about the end of the active participation in the study.

### **Premature withdrawal of subjects**

During any study period, the participant has the rights to terminate the participation in the study and to prohibit the analysis of any collected data or samples. It is considered as a withdrawal of the study, therefore the investigator must be informed.

In case of premature withdrawal, the participant will return the unused *Metformin* 850 mg tablets, provide filled questionnaires and collected stool samples to the investigator. In a case-specific manner the investigator will agree to participant on further scientific application of the results obtained from the participant during the study. Based on the observations made about the participant's health, the need for a visit to a physician or certified specialist will be considered. On the 13th day of the study the investigator will re-examine all the study subjects during in the form of phone call visit. Withdrawn subjects will not be replaced with other volunteers.

Reasons for withdrawal:

1. Moderate or severe adverse drug reactions observed.
2. Use of other medications that are incompatible with *Metformin* 850 mg or may affect the results of the study.
3. Other conditions essential for the subject.

Cases where a participant of a study is excluded from participation in a study following a sponsor or researcher's decision:

1. Incompliance with the activities specified in the protocol: lack of one or more blood or stool samples.
2. Use of undesirable medications (antibiotics, probiotics) during the trial, which may affect the study results.

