### **Study group**

The study will enroll 50 healthy volunteers of European descent (both sexes) at 18-64 years of age, meeting predefined inclusion/exclusion criteria. Recruitment of the healthy volunteers and further collection of biological samples will be carried out in cooperation with the Genome Database of the Latvian Population (LGDB). Only healthy participants will be involved in the study to avoid potential effect of contributing factors such as the use of other antidiabetic drugs or antibiotics, which may have a systemic effect on microbial composition and epigenetic gene regulation causing biased results. The pre-selected age range of the participants in the study (18-64 years) is defined based on the need for homogeneous microbial compositions among individuals [Claesson et al. 2011; Zapata and Quagliarello 2015]. The number of subjects in the study group is defined on the basis of the calculations of the statistical power of the study (at least 80%), taking into account the potential fluctuations within the size of the study group ( $\approx 2\%$ ), when subjects discontinue the participation in the study for non-research reasons. The confidence level used is  $\alpha = 0.05$ .

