### **Stool sample analysis**

The study participants will collect the stool samples by using specific collection tubes at three consecutive time points: before administration of metformin, on the day when the treatment is started (after the first dose) and after a week-long metformin treatment. During the

regular visits, the investigator or his representative will advise the participants about an optimal time for collecting stool samples. Participants will deliver the samples to LBMC during their regular visits. Samples will be collected in two aliquots, one of them will be used for the isolation of microbial DNA and subsequent metagenome and metabolite analysis, the second aliquot will be stored as a backup sample at -70 ° C in the BMC premises.

The microbial DNA will be isolated from the stool samples and further used to determine the taxonomic alterations in the composition of gut microbiome according to the 16S rRNA gene fragment sequences obtained. In addition, shotgun metagenome sequencing will be performed, providing the information about the metabolic processes and function of the gut microbiome. The alterations in the composition of gut microbiome induced by metformin will be evaluated by comparing the microbial composition of stool samples collected before the first intake of metformin and during or after administration of metformin.

**Methods:** Microbial DNA from fecal samples will be isolated using FastDNA kit for Soil (MP Biomedicals), following the manufacturer's instructions. The 16S rRNA gene fragment analysis and shotgun metagenomic sequencing (Ion Plus Fragment Library Kit, Thermo Fisher Scientific) will be performed on a large-scale parallel sequencing platform (Ion Torrent). A detailed analysis of the individual taxonomic groups of bacteria will be carried out using the Sanger sequencing method and real-time PCR. Determination of metformin and various metabolites in samples (blood and stool) will be carried out with MALDI-TOF mass spectrometers and equipment available in the Latvian Institute of Organic Synthesis (OSI): gas chromatography (FID, ECD, TCD, MSD) and liquid chromatography - tandem mass spectrometry (LC-MS / MS).

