The ability of metformin to induce alterations in the composition of gut microbiome and epigenetic gene regulation will be analyzed using biological materials (venous blood and feces) derived from three treatment-related time points: before metformin use, 10 hours after the first dose of metformin and 7 days after metformin use. For each participant of the study, alterations in the diversity and proportion of microbial taxonomic units of the gut microbiome and metabolite composition and concentrations in stool samples will be determined. In addition, metformin-induced alterations in DNA methylation and transcriptome profiles will be analyzed. Data obtained from biological samples collected before the use of metformin will be considered as a reference. By combining the results of all participants, conclusions will be drawn on the effect of metformin on the composition of gut microbiome and epigenetic regulation. Statistical data analysis will allow to determine an association between microbial composition and severity of adverse reactions, microbial composition and changes in DNA methylation or RNA expression profiles, DNA methylation profiles and drug tolerance.

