## PROBLEMS ANTICIPATED

| Deviation from the protocol                                                              | Action of participant                                                                                                                                                                  | Action of investigator                                                                       |
|------------------------------------------------------------------------------------------|----------------------------------------------------------------------------------------------------------------------------------------------------------------------------------------|----------------------------------------------------------------------------------------------|
| The participant skips an intake of Metforal 850mg tablet.                         | A double dose is not used. The deviation is fixed in the diet diary.                                                                                                                   | Deviations from the protocol are taken into account during data processing.                  |
| Participant postpones the collection of stool sample.                                    | Participant informs the investigator, marks the collection tube according to the date of sample collection, continues collection of remaining samples according to the study protocol. | The specific stool sample is excluded from the gut microbiome analysis.                      |
| Participant postpones the delivery of stool sample.                                      | The sample is delivered to BMC as soon as possible.                                                                                                                                    | Deviations from the protocol are taken into account during data processing.                  |
| Participant is not able to attend a blood donation visit in BMC.                         | Participant informs the investigator. If possible, the participant donates a blood samples in E. Gulbis laboratory.                                                                    | Ensures sample delivery to BMC and further processing according to the protocol.             |

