| Participant is not able to attend a blood donation visit in BMC or E. Gulbis laboratory. | Participant informs the investigator, continues to donate the remaining samples according to the study protocol.                                                                       | The specific blood sample is excluded from the DNA methylation and gene expression analysis. |

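### The rules for a missed or late sample conflict: one allows the participant to be excluded, another drops only the sample, and the day of the second stool sample is itself stated inconsistently

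*Protocol*

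**What the plan says.** **Missing samples.** The section Premature withdrawal of subjects lists cases in which the sponsor or researcher may decide to exclude a participant. The first is: "Incompliance with the activities specified in the protocol: lack of one or more blood or stool samples". The same section says that withdrawn subjects are not replaced.

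The table under Problems anticipated treats such events at sample level:
- A participant who can attend neither blood-donation site goes on giving the remaining samples, and "The specific blood sample is excluded from the DNA methylation and gene expression analysis".
- A participant who postpones a stool collection marks the tube with the actual date and continues, and "The specific stool sample is excluded from the gut microbiome analysis". No window is given.

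**Time of the second stool sample.** The Project summary says 24 hours after administration. Figure 1 places it on Day 5, and the visit schedule says: "Participants will be instructed to collect the second stool sample on day 5 of the study". Treatment starts on Day 4. Stool sample analysis, however, puts it "on the day when the treatment is started (after the first dose"). The text on evaluating the product gives a single set of times for blood and faeces together: "before metformin use, 10 hours after the first dose of metformin and 7 days after metformin use".

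**Context.** Under Endpoints of the study, the primary endpoint is change in gut microbiome composition, which is measured in stool. Study group plans 50 participants and allows for about 2% attrition, described as discontinuation for reasons unrelated to the research.

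**The concern.** A missed blood draw has no bearing on whether the stool samples are valid. Under the withdrawal section it can still end participation, and stool samples not yet collected are then lost. Under the table the stool series stays intact. Two investigators following the same protocol could therefore produce different data for the primary endpoint. These are rules about who stays and who keeps giving samples, so an analysis plan cannot recover samples that were never taken.

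The stool timing adds a second ambiguity. A Day 5 sample is on time under the visit schedule but late under the two passages that imply Day 4, and the only stated consequence of lateness is removal from the microbiome analysis. The table is also uneven: late delivery and skipped tablets are to be allowed for in data processing, whereas late collection leads to deletion even though the date is on the tube.

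**Working it through.** **1. The two rules side by side**

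| Event | Premature withdrawal | Problems anticipated |
|---|---|---|
| Blood sample missed | Participant may be excluded, no replacement | Participant continues; that sample leaves the methylation and expression analysis |
| Stool sample postponed | Not mentioned | Participant continues; that sample leaves the microbiome analysis |
| Stool sample absent | Participant may be excluded, no replacement | Not mentioned |

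The conflict is direct in the blood row. For stool it takes a further step: once a postponed sample has been dropped, the participant has no usable sample at that time point, and the exclusion case could then be invoked.

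**2. The second stool time**

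| Place | Time stated | Study day |
|---|---|---|
| Project summary | 24 h | 5 |
| Figure 1 | Day 5 | 5 |
| Visit schedule, 4th and 5th visits | Day 5 | 5 |
| Stool sample analysis | Day treatment starts | 4 |
| Evaluation of efficiency | 10 h after first dose | 4 |

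**3. The plan's own sample size.** The total of 50 cannot be reproduced, because no effect size, standard deviation or test is given for the power statement. Only the attrition step can be checked: 50 × 0.98 = 49 evaluable participants.

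**4. Illustration of how far the rules diverge.** Inputs from the protocol: 49 participants, 3 stool samples and 3 research blood samples each (the verification blood sample is not counted). Assumption: each sample is missed independently with probability *m*. The documents give no value for *m*.

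- Participant-level rule, all six samples required: 49 × (1 − m)^6.
- Sample-level rule, counting participants with the baseline and end-of-treatment stool pair: 49 × (1 − m)^2.

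| m | All six present | Stool pair present | Difference |
|---|---|---|---|
| 1% | 49 × 0.9415 = 46.1 | 49 × 0.9801 = 48.0 | 1.9 |
| 2% | 49 × 0.8858 = 43.4 | 49 × 0.9604 = 47.1 | 3.7 |
| 5% | 49 × 0.7351 = 36.0 | 49 × 0.9025 = 44.2 | 8.2 |

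**5. What that could mean for power.** This step is also illustrative. Take a two-sided paired t-test at 0.05 (the protocol does not state sidedness) and the standardised effect that gives 80% power with 49 participants, d = 0.41. Power comes from the noncentral t distribution with n − 1 degrees of freedom and noncentrality d√n, with n rounded. For m = 1%, 2% and 5% it is about 77%, 74% and 66% under the participant-level rule, against 79%, 78% and 75% under the sample-level rule.

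**The case against.** **The withdrawal section governs participation, not the analysis set.** It describes a decision by the sponsor or researcher, under non-compliance, and leaves use of a withdrawn participant's results to case-by-case agreement. A reader might infer that one missed blood draw deletes stool data already collected. The text does not say that. What stands is that exclusion can stop later collection, and that no criterion says when to apply it rather than the table.

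**The operative schedule is consistent.** Participants are told Day 5, so postponed most naturally means later than Day 5. A Day 4 sample would be early, and the table does not cover early samples. This makes the timing conflict largely a drafting matter, but the sections describing the stool methods and the evaluation still contradict the schedule, and no window is given.

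**The losses can be made to look larger than they are.** At m = 5%, 1 − 0.95^6 = 26.5% of participants would lack at least one sample, and a reader might set this against 5% of samples lost. Those are different units; 36 against 44 of 49 is the comparable figure. Nor should the 2% attrition allowance serve as a ceiling for these exclusions, since it covers only discontinuation for non-research reasons. The fallback laboratory for blood should also reduce missed draws.

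**Bias is not shown.** A reader might infer that deleting late stool samples tilts the result toward people without bowel change. The gastrointestinal effects listed in the risk section include diarrhoea but not constipation, and nothing links postponement to the drug. Only a possible risk that sample loss is related to tolerance remains.

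**Dropping late samples can be defended in a fixed-time design.** The last stool sample is already taken the day after the final dose, so delay adds time off drug. This argues for modelling actual time and stating a window. It does not settle which rule applies.

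**Conclusion.** The point holds in limited form. The protocol gives two incompatible outcomes for a missed blood sample and does not say which prevails; the conflict for stool is indirect. The second stool sample is set at Day 5 in the schedule and at Day 4 in two other places, and late stool samples are dropped without a stated window. Both matters bear on the data for the primary endpoint.

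The size depends on sample loss, which the documents do not give. Under independent loss the rules differ by about 2, 4 or 8 participants out of 49 at 1%, 2% or 5% per sample, and the difference vanishes as loss approaches zero. The power figures rest further on a paired t-test and an effect chosen to give 80% power. No direction of bias is claimed.

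**What to change.** 1. Reconcile the withdrawal section with the table so that a missed sample is left out of the matching analysis only, and the participant's other samples are still collected and analysed. The mixed-model software lme4, already named in the statistical methodology, accommodates unequal numbers of samples per person. Whether exclusion under the withdrawal section also stops treatment is for the sponsor to reconcile; no rule is proposed here.
2. Align Stool sample analysis and the evaluation text with the Day 5 schedule, give blood and stool separate times, and state a collection window for stool.
3. Keep dated late on-treatment stool samples with actual time since dose as a covariate, at least as a sensitivity analysis. A baseline sample must still precede the first dose.

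The cost is protocol wording, recording the collection time, and one covariate. The downside is slightly less uniform sampling times, which can be examined by comparing results with and without the late samples.
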